## Abstract

**Background:**

Homeless services expend considerable resources to provide for service users’ most basic needs, such as food and shelter, but their track record for ending homelessness is disappointing. An alternative model, Housing First, reversed the order of services so that homeless individuals are offered immediate access to independent housing, with wraparound supports but no treatment or abstinence requirements. Although the evidence base for Housing First’s effectiveness in ending homelessness is robust, less is known about its effectiveness in promoting recovery.

**Objective:**

The objective of this research is to compare rehabilitation- and recovery-related outcomes of homeless services users who are engaged in either Housing First or traditional staircase services in eight European countries: France, Ireland, Italy, the Netherlands, Poland, Portugal, Spain, and Sweden.

**Methods:**

A mixed methods, multi-site investigation of Housing First and traditional services will compare quantitative outcomes at two time points. Key rehabilitation outcomes include stable housing and psychiatric symptoms. Key growth outcomes include community integration and acquired capabilities. Semistructured interviews will be used to examine service users’ experiences of environmental constraints and affordances on acquired capabilities to identify features of homeless services that enhance service users’ capabilities sets. Multi-level modelling will be used to test for group differences—Housing First versus traditional services—on key outcome variables. Thematic analysis will be used to understand the ways in which service users make sense of internal and external affordances and constraints on capabilities.

**Results:**

The study is registered with the European Commission (registration number: H2020-SC6-REVINEQUAL-2016/ GA726997). Two press releases, a research report to the funding body, two peer-reviewed articles, and an e-book chapter are planned for dissemination of the final results. The project was funded from September 2016 through September 2019. Expected results will be disseminated in 2019 and 2020.

**Conclusions:**

We will use the findings from this research to formulate recommendations for European social policy on the configuration of homeless services and the scaling up and scaling out of Housing First programs. From our findings, we will draw conclusions about the setting features that promote individuals’ exits from homelessness, rehabilitation, and recovery.

**International Registered Report Identifier (IRRID):**

RR1-10.2196/14584

## Introduction

### Background

The personal costs of homelessness are significant and multidimensional. Individuals who experience chronic homelessness are more likely to have mental health and/or substance misuse problems, experience victimization, and have fewer opportunities to develop positive identities or to participate in valued social activities than the general population [1-3]. European social policies that reverse homelessness rather than manage it have been quite limited and, as one consequence, homeless services expend considerable resources to provide for service users’ most basic needs, such as food and shelter. Increasingly, researchers have begun to direct their efforts toward understanding how to improve the structure of homeless services so they can do more to reverse homelessness and ameliorate its costs to individuals and society [4,5]. The aim of this study is to examine the relationship of homeless services settings to service users’ recovery experiences.

A growing body of evidence suggests that the traditional structure of homeless services, which follows a model of care that is variously referred to as “treatment first,” “continuum of care,” or “staircase,” limits homeless individuals’ potential for recovery in terms of both rehabilitation and growth [6]. A deficits model of homelessness, in which attributions for chronic homelessness focus on individuals’ mental illness, substance misuse, and poor decision making, underpins the structure of treatment-first programs [7]. Consequently, the setting features of traditional services encourage compliance through treatment and sobriety prerequisites, a range of house rules and regulations, and the promise of independent accommodation [8]. Failure to comply with setting rules can result in moves back down the continuum to more restrictive housing arrangements or even eviction [6,9].

The underwhelming track record of traditional services was highlighted and critiqued by both the consumer and recovery movements; both questioned the assumptions that underpin the treatment-first model and its setting features [10,11]. An alternative model of homeless services delivery that is based in principles of consumer choice, empowerment, and recovery was introduced in New York City in 1992 [12,13]. Originally designed to serve chronically homeless adults with serious mental illness who may also have a co-occurring substance use disorder, Housing First reversed the order of services to provide independent, scatter-site apartments with no treatment preconditions or abstinence requirements. Support services are tailored to clients’ preferences and needs and are provided 24/7 by either Assertive Community Treatment or Intensive Case Management teams. Housing First programs typically require service users to meet weekly with staff members, contribute 30% of their income toward the cost of rent, and comply with a standard lease agreement. Despite significant opposition to the model and skepticism from service providers and stakeholders [11,14], initial tests of Housing First returned impressive rates of stable housing [15,16] and cost-effectiveness [17,18] compared to traditional services. Critics’ fears about increased substance use and psychiatric symptoms have not been supported by research findings [14,19]. There is evidence that greater consumer choice afforded to individuals in Housing First programs fosters greater personal mastery, which, over time, predicts fewer psychiatric symptoms [20].

Since its first implementation, Housing First has been disseminated across the globe. The first randomized and controlled trial was conducted in New York City, in which Housing First was compared to treatment as usual [21,22]. The largest randomized trial of Housing First thus far was conducted in Canada [23] and a third randomized trial was conducted in France [24]. The positive outcomes of these trials spurred widespread dissemination and nonexperimental pilot and demonstration projects [4,5]. Although the exact number of Housing First programs is unknown, it has been widely disseminated in North America, Europe, Australia, and New Zealand [25,26]. Despite Housing First’s widespread reach and strong evidence base, most European homeless services continue to follow the treatment-first model [27]. Researchers and practitioners continue to work together to expand the evidence base for Housing First through rigorous experimental and observational trials. This study’s comparison of Housing First and traditional services in eight European countries aims to demonstrate not only that Housing First reverses homelessness in these different contexts, but to identify the setting features that explain how it works and, in doing so, produce translational findings that may have widespread influence in policy and practice.

### Homeless Service Features and Service Users’ Recovery Experiences

When homeless services providers, stakeholders, and policy makers advocate for new Housing First programs, or for the reconfiguration of traditional treatment-first programs toward *housing-led* services, they tend to be motivated by ambitions to develop programs that facilitate service users’ exits from homelessness; they are also motivated to promote service users’ empowerment, personal growth, and freedom to participate in valued activities and roles [28,29]. Taken together, this goal can be conceptualized in terms of facilitating “a life worth living,” which is defined in the capabilities approach as an individual’s freedom to do and to be [30,31]. More specifically, capabilities are the opportunities that are realistically available to a person, which are determined by environmental and internal factors. Environmental factors can operate as either affordances or constraints on an individual’s ability to develop, maintain, or exercise internal capacities to freely enact desired behaviors. Internal affordances and constraints include, but are not limited to, a person’s intellectual abilities, physical and mental health, relationship to alcohol and illicit substances, skills, traits, motivations, and characteristic adaptations. For example, childhood poverty and neglect are environmental constraints that undermine an individual’s ability to obtain adequate education or develop the kinds of intra- and interpersonal skills required for a range of occupations, roles, and activities [32]. Functionings are those capabilities that a person freely chooses to enact.

Situations of extreme social exclusion such as homelessness are environmental constraints; that is, they are forms of inequality and unfairness that block an individual’s opportunities to develop new internal affordances or restore affordances that may have been lost. Indeed, homelessness has been described as capabilities failure [28] and capabilities deprivation [33]. Homeless services settings are important mediating structures that can broaden or constrict the environmental affordances on an individual’s freedom to do or to be [28,29]. Homeless services can also facilitate or constrain a person’s opportunities to develop the kinds of internal affordances, such as education, skills, psychiatric symptom management, or effective self-regulation of substance use, that are prerequisites to functionings in valued activities or socially valued identities and roles [28,29]. We aim to identify the setting features of homeless services (ie, environmental affordances and constraints) that affect service users’ abilities to develop useful skills and abilities (ie, internal affordances) that broaden their capabilities sets and enhance their central functionings.

Although a growing evidence base reports the effectiveness of Housing First interventions for reducing homelessness for adults with complex support needs [22,34], there is more to learn about the specific setting features that operate as mechanisms through which these results may be achieved. Three important setting features are choice over housing and services, housing quality, and satisfaction with services. Previous research demonstrated that participants who were engaged with Housing First services consistently reported greater choice, better housing quality, and more satisfaction with services [5,18,35,36]. Among other important outcomes, consumer choice predicts greater mastery, stable housing, fewer psychiatric symptoms, and less problem-related substance use [15,16,35,37]. Perceived housing quality and service users’ satisfaction with their input into the treatment and services they receive have both been associated with positive recovery-related outcomes, including engagement with supports [38] and reduced substance use [39].

### This Study

In this paper, we describe the protocol for the Service Users’ Experiences Study, one prong of a larger project called *Homelessness as Unfairness*, or HOME_EU, which takes an ecological approach to understanding long-term homelessness in Europe. Citizens’ attitudes, social policy, service providers’ experiences, and service users’ experiences are each investigated in separate empirical studies. Our aim is to combine findings from the four studies into a body of translational knowledge that can be used to enhance European social policies so that countries may move beyond managing homelessness toward ending it.

In the Service Users’ Experiences Study, we aim to investigate the features of homeless services hypothesized to function as key environmental affordances and constraints on service users’ recovery and capabilities. We aim to understand how persistent homelessness thwarts individuals’ basic liberties and equality aspirations. The capabilities approach [40] provides the theory-driven framework that guides our work on this project, which we will use to interpret our findings and propose practical guidelines to promote social justice in homeless policy and homeless services settings. The HOME_EU Consortium will combine findings from the Service Users’ Experiences Study with findings from our studies with citizens, policy makers, and service providers. This will produce a translational multidimensional conceptualization of homelessness across eight European countries that will inform social policy at the European and national levels and encourage best practices in homeless services that promote recovery and inclusion in civil society.

### Research Design

Our study uses a mixed methods design and is being conducted in eight European countries: France, Ireland, Italy, Poland, Portugal, the Netherlands, Spain, and Sweden. Our design is correlational and not randomized. We will recruit participants who are already engaged with either Housing First or traditional services and collect quantitative data via questionnaires at two time points: baseline (T0) and follow-up (T1). This will allow us to control for baseline nonequivalence on demographic characteristics and other individual differences, such as lifetime homelessness, length of time in current accommodation, alcohol and substance use, education, and physical health. A subset of participants from each country who completed the questionnaires will complete an in-depth, qualitative, capabilities interview. In this paper, we describe the core procedures and methods that will be completed across all eight study sites.

### Objectives

The first objective of this study is to compare Housing First and traditional services regarding key service and support features hypothesized to promote recovery in terms of both rehabilitation and growth. The second objective is to explore participants’ subjective experiences of environmental and internal affordances and constraints on their functionings and capabilities, especially in the areas of valued social roles, activities, relationships, and responsibilities [28,30,31,41,42].

The specific objectives of the Service Users’ Experiences Study are as follows:

Determine whether Housing First and traditional services are differentiated on key setting features previously demonstrated to be linked to recovery indicators.Determine whether implementations of Housing First across eight different European contexts are consistent with one another and consistently differentiated from traditional services on these key setting features.Determine whether setting features predict recovery outcomes at the second time point (T1), controlling for baseline (T0) scores.Understand service users’ subjective experiences of their own recovery of human rights, defined as capabilities, and the ways in which these experiences are afforded or constrained by their engagement with Housing First or traditional homeless services.

## Methods

### Quantitative Methods and Analysis

#### Recruitment and Data Collection

##### Overview

Consortium partners in each country will use their existing links to Housing First programs and traditional homeless services to recruit participants to the study. Partners in France, Ireland, Italy, Portugal, and Spain have been directly involved in Housing First pilot and demonstration projects, so they may directly contact participants to invite them to participate in this research. Researchers will liaise with key workers, team leaders, and program managers employed in either Housing First programs or traditional services for assistance with recruiting additional participants to the study so that we can achieve our target sample size.

##### Questionnaire Administration

Research interviewers will meet individually in a quiet location chosen by participants. After a short ice-breaker conversation intended to build rapport, the researcher will explain the study and obtain informed consent before administering the questionnaire. The 13 measures included in the baseline questionnaire are presented in Table 1. Research interviewers will read each item to participants using a standardized procedure and record participants’ responses on the questionnaires. When the questionnaire is complete, the researcher will ask permission to contact the person to complete the questionnaire 6 months later.

##### Data Management

Participants’ responses will be entered into a standardized SPSS, version 24.0 (IBM Corp), data file template that will be used in every site to ensure equivalence of data entry. Several steps will be, or have been, taken to ensure data quality. First, we will administer measures previously used with this population to maximize measure validity and reliability. Second, interviewers will follow a data entry protocol and receive ongoing support via telephone, email, and face-to-face meetings. Third, the type and range of data values and mandatory entry were built into entry fields in the database. Fourth, questions from interviewers were fielded centrally and decision rules were made where necessary and circulated to all partners. Fifth, the authority to change data elements will be restricted to a small team [43].

#### Sample Size and Retention Plan

Our target sample for the second time point (T1) is 480 participants (Housing First, n=240, and traditional services, n=240). Because we anticipate attrition between T0 and T1, we intend to oversample each group at baseline. Based on prior research [22,36], we anticipate greater attrition in the traditional services group, so we aim to sample 38 Housing First participants and 45 traditional service participants in each of the eight countries at T0 (N=664). In order to maximize follow-up, we have adapted Stefancic and colleagues’ guidelines [44]. Specifically, at the baseline data collection meeting, researchers will ask participants to predict where they will be living 6 months later; to provide a range of contacts for family members, friends, and service providers; and to contact the research team if they change their phone number or move to a new residence. Participants will be compensated with a €20 shopping voucher for each questionnaire and interview they complete.

#### Participants

To be eligible to participate in this study, potential participants must meet the following inclusion criteria: be 18 years of age or older to legally consent to participate; have spent 6 or more months homeless in their lifetime; be currently engaged with homeless services, either Housing First or traditional services; and be sufficiently proficient in the language of the country in which they reside to understand all the questionnaire items. Exclusion criteria include the following: unable to provide consent at time of data collection because of active psychosis or inebriation, less than 18 years of age, have insufficient proficiency in the questionnaire language, have spent fewer than 6 months homeless in their lifetime, and not currently engaged with a homeless service.

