## Discussion

We will use the findings from this research to formulate recommendations for European social policy on the configuration of homeless services and the scaling up and scaling out of Housing First programs. From our findings, we will draw conclusions about the setting features that promote individuals’ exits from homelessness, rehabilitation, and recovery.

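### Recruiting only current service users makes baseline housing status largely a product of arm, so the planned housing comparison cannot by itself show that Housing First reverses homelessness

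*Protocol article*

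**What the plan says.** - **Who is sampled.** Research Design: "We will recruit participants who are already engaged with either Housing First or traditional services". Participants repeats this as an inclusion criterion ("be currently engaged with homeless services, either Housing First or traditional services") and lists as an exclusion being "not currently engaged with a homeless service". The article describes no cohort enrolled at service entry.
- **What the services are.** Introduction, Background: "Housing First reversed the order of services to provide independent, scatter-site apartments with no treatment preconditions or abstinence requirements". The same section describes the traditional model as one in which independent accommodation is promised to those who comply, and in which failure to comply can lead to more restrictive housing or eviction.
- **The outcome.** Abstract, Methods: "Key rehabilitation outcomes include stable housing and psychiatric symptoms". Table 1 lists housing status at both waves, measured with a study-made instrument based on a European homelessness typology.
- **The analysis.** Statistical Analysis plans to compare the two groups on rehabilitation outcomes at baseline and at follow-up (T1). It then models T1 with control for T0 scores, country and demographic factors. Follow-up is at 6 months (Questionnaire Administration).
- **The intended conclusion.** The Introduction says that this comparison "aims to demonstrate not only that Housing First reverses homelessness in these different contexts". The Discussion says "we will draw conclusions about the setting features that promote individuals’ exits from homelessness", and the Abstract's Conclusions say the same, alongside recommendations for European social policy.
- **The stated caveat.** Research Design: "Our design is correlational and not randomized".

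**The concern.** A current Housing First user has, in the usual case, already received the outcome as the content of the service. A current user of traditional services is observed while still on the way to it. A difference in housing level at T0 therefore mixes three things: what the service is, any effect it had on people before T0, and who is still enrolled. Nothing described in the article separates them.

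T1 inherits the problem. The unadjusted T1 difference carries the T0 difference forward. The adjusted one conditions on a variable that arose after exposure, so it removes the initial rehousing, which is the step that would reverse homelessness. No model recovers people who left before T0. At stake is whether the housing result can support policy advice in eight countries as evidence that Housing First ends homelessness.

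**Working it through.** **1. The plan's own figures.** Sample Size and Retention Plan: 8 × 38 = 304 Housing First and 8 × 45 = 360 traditional, total 664, as stated. With 240 per arm at T1, implied attrition is 1 − 240/304 = 21.1% and 1 − 240/360 = 33.3%. The article states no housing rate, effect size or power, so there is no housing calculation to reproduce.

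**2. What selection alone could produce.** Every rate here is an assumption.
- q: share housed, equal in both entry cohorts (no true difference).
- r: chance of still being engaged at T0 for Housing First members who lost housing, relative to those who kept it. The same r applies to traditional-services members who gained housing, relative to those who did not.
- Housed at T0: p(HF) = q / [q + (1 − q)r]; p(TS) = qr / [qr + (1 − q)].
- Over six months, in both arms, 90% of the housed stay housed and 10% of the unhoused become housed. Housed at T1 = 0.9p + 0.1(1 − p) = 0.1 + 0.8p.
- T1 difference = 0.8 × [p(HF) − p(TS)].

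Example, q = 0.5 and r = 0.5: p(HF) = 0.5/0.75 = 66.7%; p(TS) = 0.25/0.75 = 33.3%; T1 63.3% v 36.7%, a spurious 26.7 points.

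| r (q = 0.5) | T0, HF v TS | T1, HF v TS | Difference, points | Rejection probability |
|---|---|---|---|---|
| 0.1 | 90.9% v 9.1% | 82.7% v 17.3% | 65.5 | about 100% |
| 0.3 | 76.9% v 23.1% | 71.5% v 28.5% | 43.1 | about 100% |
| 0.5 | 66.7% v 33.3% | 63.3% v 36.7% | 26.7 | about 100% |
| 0.8 | 55.6% v 44.4% | 54.4% v 45.6% | 8.9 | about 50% |
| 1.0 | 50% v 50% | 50% v 50% | 0 | 5% |

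With q = 0.3 or 0.7 the differences at r = 0.1, 0.3, 0.5 and 0.8 are 61.6, 37.9, 22.8 and 7.5 points. The rejection probabilities are for an unadjusted two-proportion test with 240 per arm and ignore clustering within programmes.

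**3. The sign is not fixed.** Values of r below 1 describe only departures that favour Housing First. If Housing First successes and traditional-services failures are the likelier leavers, r exceeds 1. At r = 1/0.8 = 1.25 and q = 0.5: p(HF) = 0.5/1.125 = 44.4%, p(TS) = 0.625/1.125 = 55.6%, T1 difference −8.9 points.

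**4. What T0 adjustment does.** In this example, stratifying by T0 status gives 90% v 90% among the housed and 10% v 10% among the unhoused. That is correct for six-month transitions, but it says nothing about how people came to be housed before T0. Overlap may also be thin. At q = 0.5 and r = 0.1, about 28 of 304 Housing First participants are unhoused at T0 (304 × 0.091) and 33 of 360 traditional-services participants are housed (360 × 0.091). If attrition is unrelated to housing, about 28 × 240/304 = 22 and 33 × 240/360 = 22 remain at T1. At r = 0.5 the T0 counts are 101 and 120.

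**The case against.** The strongest reply has four parts.

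- **The design is openly correlational, and ending homelessness is not a listed objective.** The Objectives section concerns setting features, their consistency, their prediction of T1 recovery, and subjective experience. This lowers the weight of the point. It does not remove it, because stable housing is named as a key outcome for the group comparison and the Introduction states the stronger aim. The caveat covers non-randomisation and baseline non-equivalence, not selection by continued engagement.
- **Direction.** A reader might infer that excluding leavers must favour Housing First. The documents do not support that. Evicted traditional-services users are lost too, which flatters that arm, and so are Housing First users who succeeded and disengaged. This part stands.
- **Certainty and size.** A reader might infer that arm fixes housing status outright, or that a very large difference would appear whatever the true effect. The article gives no T0 housing rates, does not show how the housing instrument is scored, and does not say that losing the apartment ends engagement with Housing First support. Any specific figure restates its own assumptions. This part stands as well.
- **Part of the remedy is planned.** T1 is analysed with T0 control, participants who move are to be traced, and nothing says that people who leave a service after T0 are dropped. That is right, and it is why the fix is cheap. It does not reach losses before T0.

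**Conclusion.** The point holds in a bounded form. Given the eligibility rule and the article's own description of the two models, T0 housing status is largely determined by arm, and departures before T0 are selective. The planned difference in housing level at T0 or T1 therefore cannot by itself demonstrate that Housing First reverses homelessness. Adjusting for T0 housing changes the question to six-month retention or exit, probably with limited overlap.

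The size is unknown. The 0 to 65 point range at q = 0.5 rests on an assumed common entry rate, assumed relative engagement r from 1 down to 0.1, and assumed common transitions. It shows sensitivity to selection and is not an estimate of bias in this study.

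The same selection may touch symptoms, substance use and the growth outcomes, so these cannot be treated as exempt. Whether the services differ on setting features (the first two objectives) is less affected.

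**What to change.** 1. Do not interpret the Housing First v traditional-services difference in housing-status level as an effect on ending homelessness.
2. Report T0-to-T1 housing transitions by T0 status: retention among those independently housed at T0, and moves to independent housing among those who were not. Show the number in each arm and stratum.
3. State that participants who leave a service after T0 stay in their T0 arm.
4. Reword the Introduction's aim, the Abstract's Conclusions and the Discussion so that the housing statements cover association and six-month retention or exit among current users.
5. State selection by continued engagement as a limitation for the housing outcome and for the other outcomes.

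**Cost.** No additional data, since housing status is planned at both waves. The housing claim becomes narrower, and some strata may be too small for a useful between-arm comparison.
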